##### Motivation to Change

Participants’ motivation to change will also be measured with the following item adapted for this study: *Which of the following statements best describes your view of your current relationship problems* [51]? Participants will respond on a four-point Likert-style scale ranging from *I don’t think I have relationship problems and therefore nothing should be done about it* (coded as 0) to *I know I have relationship problems, and I am here to take action to work on them now*.

### Data Analysis

In an effort to reduce computational complexity, rather than using individual responses, responses from both members of the couple will be combined in the average score for the couple for each of the continuous predictor variables listed above as well as the continuous outcome variable (ie, relationship satisfaction).

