### Participants

A total of 226 couples were randomly assigned to the OurRelationship coach condition, 145 couples were assigned to the OurRelationship contingent coach condition, and 145 couples were assigned to the OurRelationship automated (ie, email only) condition. Similarly, 222 couples were assigned to the ePREP coach condition, 143 couples were assigned to the ePREP contingent coach condition, and 143 couples were assigned to the ePREP automated (ie, email only) condition. A total of 224 couples were assigned to the waitlist control condition. In total, 4 individuals from the OurRelationship coach condition, 2 from the OurRelationship contingent coach condition, and 2 from the OurRelationship automated condition asked to discontinue and have their data removed from the study. Furthermore, 3 individuals from the ePREP coach condition, 2 from the ePREP contingent coach condition, and 3 from the ePREP automated condition asked to discontinue and have their data removed from the study.

In total, 47.5% (1178/2480) of the sample identified as male, and 52.5% (1302/2480) of the sample identified as female. The average length of the relationship was 5.74 years (SD 5.18). Most of the participants reported belonging to an opposite-gender relationship (2318/2480, 93.47%), and a smaller percentage were in same-gender relationships (162/2480, 6.53%). Most participants identified as White non-Hispanic (1520/2480, 61.29%), fewer identified as Black (434/2480, 17.5%), White Hispanic (279/2480, 11.25%), Black Hispanic (28/2480, 1.13%), American Indian or Alaskan Native (23/2480, 0.93%), Asian (17/2480, 0.69%), Hawaiian or Pacific Islander (4/2480, 0.16%), and Biracial (86/2480; 3.47%); and 3.59% (89/2480) of participants belonged to a race that was not listed. Furthermore, 6.81% (169/2480) of participants did not have a degree or diploma, 12.3% (305/2480) had earned a general education diploma, 14.23% (353/2480) had completed high school, 8.23% (204/2480) had a technical or vocational certification, 22.54% (559/2480) had some college degree, 8.83% (219/2480) had graduated with an associate’s degree, 10.69% (265/2480) had a bachelor’s degree, and 2.38% (59/2480) had a master’s or advanced degree.

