### Measures: Predictor Variables

#### Demographic Variables

Although support for demographic variables and their relationship to treatment adherence varies, a host of demographic variables will be included as candidate predictor variables. Predictor variables include race, ethnicity, household income, age, gender, as well as identifying as a same-gender couple.

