#### Measures of External Stress

##### Overview

In addition to including predictors of relationship well-being, the inclusion of measures assessing external stress has been shown to be a consistent predictor of treatment adherence. In addition, as this is measured at the individual level, this may highlight within-relationship differences that may aid in the prediction of treatment nonadherence and satisfaction gains. This study intends to measure psychological distress and general health using the following measures:

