##### General Health

Impacts on the physical well-being (eg, a chronic illness) of one individual may prevent both members of the dyad from completing the program. To assess general health, this study intends to use a single-item measure of general well-being on a Likert-style scale developed by the ACF (ie, *In general, how would you describe your health*).

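### Averaging the two partners discards the within-couple differences that the protocol says may help predict non-completion

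*Protocol article*

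**What the plan says.** The Data Analysis section sets one rule for all aims. The reason comes first: "In an effort to reduce computational complexity, rather than using individual responses". The rule follows: "responses from both members of the couple will be combined in the average score for the couple for each of the continuous predictor variables". The same rule applies to relationship satisfaction as the continuous outcome. No partner difference, lower or higher partner value, or partner-specific column is mentioned.

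The Overview under Measures of External Stress gives a reason for including those measures that depends on separate partner scores: "as this is measured at the individual level, this may highlight within-relationship differences that may aid in the prediction of treatment nonadherence and satisfaction gains". General Health, listed under the same heading, gives a one-partner reason: a health problem "of one individual may prevent both members of the dyad from completing the program".

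The averaged inputs feed everything downstream: the random forests of Aim 1, the variable importance of Aim 2, and the predicted between-condition differences of Aim 3.

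**The concern.** The measure sections and the analysis rule do not fit together. Two sections say that a difference between partners, or one partner's bad state, may predict who fails to finish. The analysis section then reduces each continuous measure to a couple mean, in which that information is gone or diluted. No fuller description of the random forest could repair this, because the loss occurs before any model is fitted.

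What is at stake is prediction accuracy and the reading of variable importance for the external-stress measures. If discordant couples drop out more often, the planned models cannot show it, and a modest importance for stress or health could reflect the summary chosen and not the construct. External stress is one of only two predictor groups for which the article states a hypothesis.

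**Working it through.** **1. Measures affected.** Four measures stand under external stress: psychological distress, perceived stress, chaos and general health. I assume that the single Likert item and the checklist (scored as a count) are treated as continuous, so that the averaging rule covers them.

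**2. What the mean keeps.** Partner scores of 1 and 5 give mean 3 and difference 4. Partner scores of 3 and 3 give mean 3 and difference 0. After averaging, the two couples are identical.

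**3. Share of variance discarded.** Let the partners' scores X1 and X2 have variance 1 and correlation r. The article does not give r, so it is assumed over a range. Write M = (X1 + X2)/2 and D = (X1 − X2)/2. Then:

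- Var(M) = (1 + r)/2, Var(D) = (1 − r)/2 and Cov(M, D) = 0.
- Each individual score is M + D or M − D, so its variance splits exactly into these two parts.
- Averaging keeps the first part and drops the second, (1 − r)/2.

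| Assumed r | Share discarded |
|---|---|
| 0.2 | 0.8/2 = 40% |
| 0.4 | 0.6/2 = 30% |
| 0.6 | 0.4/2 = 20% |

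Because M and D are uncorrelated, the mean explains none of the signed difference.

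**4. How much of a worse-partner effect survives.** The higher score is M + |D|. Under bivariate normality M and D are independent and Var(|D|) = Var(D)(1 − 2/π), with 1 − 2/π = 0.363. The share of variance in the higher score that the mean captures is

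R² = [(1 + r)/2] / [(1 + r)/2 + 0.363 (1 − r)/2].

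- r = 0: 0.50/(0.50 + 0.182) = 0.73
- r = 0.3: 0.65/(0.65 + 0.127) = 0.84
- r = 0.5: 0.75/(0.75 + 0.091) = 0.89

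By symmetry the same holds for the lower score, where low is worse. As correlations, the values run from 0.90 at r = 0.2 to 0.96 at r = 0.6.

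**5. Is computational complexity a real constraint?** From the Participants section, the six program conditions hold 226 + 145 + 145 + 222 + 143 + 143 = 1024 couples. With the 224 waitlist couples this gives 1248, the article's total. The candidate list has 6 demographic items, 7 relationship measures (baseline satisfaction, breakup potential, commitment, biggest problem, conflict, emotional support, violence), 4 external-stress measures and 2 motivation measures, 19 in all. One added term for each external-stress measure makes 23. That is a light load for a random forest. The article itself plans to interact every predictor with coaching and program in Aim 1.

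**The case against.** The best defence is that the hypothesis concerns level: lower stress and higher motivation should predict adherence and gains. The couple mean tests that directly, and if both partners matter equally it is the right summary. The article says only that differences may aid prediction, and the mean retains most of the worse-partner signal. Limiting the number of predictors is also sensible when the within-group models use 448, 288 and 288 couples, or 143 to 226 each if split by program. All of this stands. It limits the size of the point and argues for few added terms. It does not reconcile the measure sections with the averaging rule.

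A reader might infer more, and the document does not support it:

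- **That averaging makes gender uninformative.** The demographic list reads "Predictor variables include race, ethnicity, household income, age, gender, as well as identifying as a same-gender couple", but the averaging rule covers continuous predictors only, and no couple-level coding of gender is stated. Opposite-gender couples (2318/2480 = 93.47% of participants) have one man and one woman however partners are coded. Any lack of information there comes from using the couple as the unit, which should be kept.
- **That education and relationship length must be added.** Both were collected ("The average length of the relationship was 5.74 years"), but the choice of candidates contradicts nothing. The article calls the evidence on education mixed and does not discuss relationship length as a predictor.
- **That completion is known to require both partners.** The Program Completion section codes the couple without stating such a rule. The Results section reports completion over counts of individuals, with odd numerators such as 155/288 and 157/288.
- **That the plan favours a false null, or that motivation is equally affected.** The figures in the working show blunting, not loss, for a worse-partner effect. The motivation sections give no within-couple rationale.

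**Conclusion.** The point holds in a narrow form. For the external-stress measures, including general health, the stated analysis cannot use the between-partner information that the article gives as part of the reason for including them. The signed difference is lost completely: 20% to 40% of individual-score variance at assumed partner correlations of 0.6 to 0.2. A worse-partner effect is weakened, with about 73% to 89% of that partner's score variance still captured at assumed correlations of 0 to 0.5.

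These figures rest on equal partner variances, on assumed correlations and, for the second range, on normality. They describe information in the predictors. How much prediction accuracy would be gained cannot be derived from the document, and the gain could be small. The stated reason for averaging is weak at this scale. This is a worthwhile, cheap improvement and not a flaw that undermines the study.

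**What to change.** Keep the couple as the unit of analysis and the couple mean as a predictor. At least for psychological distress, perceived stress, chaos and general health, add the absolute difference between partners. The lower and higher partner values are an alternative, but the mean is an exact linear function of those two, so the follow-up regression should not contain all three. Neither rationale depends on which partner is worse off, so dropping the sign of the difference is acceptable. If the authors prefer to keep means only, they should revise the rationale in the two measure sections and give a better reason for averaging.

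Write the choice into the Open Science Framework preregistration, which the Procedure section describes as still to come. The Results section says that only completion rates have been analysed so far.

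The new terms derive from data already collected. The cost is a modestly longer candidate list (19 to 23), with more interaction terms in the Aim 1 comparison and more candidates for the follow-up regressions. It is most noticeable if six separate models of 143 to 226 couples are built. Limiting the added terms to these four measures contains it.

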#### Data Analysis Plan for Aim 1: Examining the Prediction Accuracy of the Within-Group Models Using the Random Forest Algorithm

The first research question asks: how well can one predict program completion and anticipated gains within (1) the full-coach condition, (2) the automated coach condition, and (3) the contingent coach condition? To ensure that the different programs do not account for a substantial portion of the variance when predicting program completion or changes in relationship satisfaction, a test will be performed where 2 models will be created and compared. In the first model, all predictors will be interacted with the level of coaching (full, contingent, and automated) and the program assignment (ie, OurRelationship and ePREP) resulting in Predictor×Treatment×Coaching interactions. However, the second model will maintain all predictors by coaching interactions but drop all program assignment interactions (ie, resulting in only Predictor×Coaching interactions). Next, the root mean square error (RMSE) between the 2 models will be compared. If the null hypothesis does not get rejected (H_0_: RMSE_Model 1_ = RMSE_Model 2_), program assignment will be ignored resulting in 3 conditions (full, contingent, and automated coaching), which will be used in the proceeding aims. If the interactions account for a significant portion of the variance (H_a_ = RMSE_Model 1_ ≠ RMSE_Model 2_), independent models will be built by treatment (ie, OurRelationship or ePREP) and coach condition (full, automated, and contingent) resulting in 6 models: OurRelationship full coach, OurRelationship automated coach, OurRelationship contingent coach, ePREP full coach, ePREP automated coach, and ePREP contingent coach, which will be used in the proceeding aims.

These models will be built using the random forest algorithm [52]. The random forest algorithm reduces overfitting by bootstrapping or fitting several different trees to subsets of the sample to inform the predictions (ie, bagging) [52]. Once the ensemble of trees is generated, the outputs from all the trees are aggregated, and the prediction is generated. Its ability to predict treatment outcomes for individuals and couples has been proven in several precision medicine studies [13,14]. Thus, in the first aim of this study, the random forest algorithm will be used to accurately predict the within-group likelihood that a couple completes the OurRelationship and ePREP programs in (1) the full-coach condition, (2) the automated coaching condition, and (3) the contingent coach condition as well as the magnitude of their gains in relationship satisfaction. The model characteristics address the model performance on the test data set*.* For binary outcomes (program completion), the model characteristics used to evaluate the validity of the model include sensitivity, specificity, positive predictive value, and negative predictive value of the model built on the test data set (Figure 1). Model sensitivity is measured by the percentage of true positives (ie, a/a+c). Model specificity is the percentage of true negatives (ie, d/d+b). A model’s positive predictive value yields a positive test result and the probability that the participant will complete the program (ie, a/a+b). Finally, a model’s negative predictive value yields negative test results and the probability that the participant will not complete the program (ie, d/d+c). Good models for binary outcomes include models whose sensitivity, specificity, positive predictive value, and negative predictive value are closest to 1. For continuous outcomes (ie, improvements in relationship satisfaction), model accuracy will be evaluated using the RMSE. The RMSE is a measure of absolute fit and is the square root of the variance of the residuals; smaller values indicate better fit.

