**Objective:**

The aim of this study is to use within-group models to create an algorithm to assign future couples to different programs and levels of coach contact, identify the most powerful predictors of treatment adherence and gains in relationship satisfaction *within* 3 different levels of coaching, and examine the most powerful predictors of treatment adherence and gains in relationship satisfaction *among* the 3 levels of coach contact.

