#### Data Analysis Plan for Aim 2: What Are the Most Important Within-Group Predictors?

The second research question is: what are the most powerful predictors of treatment adherence and gains in relationship satisfaction within (1) the full-coach condition, (2) the automated coach condition, and (3) the contingent coach condition? If, in aim 1, the interaction terms result in a lower RMSE, better sensitivity, or better specificity, models will be constructed based on treatment assignment (ie, OurRelationship or ePREP) and coach assignment (ie, full, contingent, or automated). One statistically powerful way to test the most potent predictors of treatment adherence and gains is through the use of variable importance (VIMP). VIMP is a nonparametric approach within the random forest algorithm, which can help investigators identify which variables play a key role in predicting a binary (eg, program completion) or continuous (eg, improvements in relationship satisfaction) variable [53]. VIMP has been calculated in many ways in the past; however, one way that has shown promise has been through permutation (ie, Briemen–Cutler) importance [53]. This method randomly changes a given variable’s out-of-bag data and compares and averages the permuted prediction error with the original error resulting in VIMP [53]. This process not only helps identify which variables play a key role in prediction but also overcomes issues of overtesting using bootstrapping. Recent studies have used these out-of-bag estimates to generate CIs to test whether a variable has a meaningful effect in predicting an outcome with great success [53]. Indeed, these studies have suggested that 95% CIs that do not include zero will be assumed to have reliable predictors [53]. After identifying the most powerful predictors using VIMP, a multiple regression model will be estimated using the reduced set of variables to aid in the interpretation of the main effects, helping clinicians identify predictors of treatment adherence and gains.

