#### Data Analysis Plan for Aim 3: Predicting Between-Group Treatment Outcomes

Assuming that the models from the previous aim have levels of prediction accuracy, each of the within-group models will be used to generate predicted outcomes for each couple’s likelihood of adhering to the program as well as their treatment gains, creating counterfactual estimates of program completion and treatment gains as if each couple in the data set completed each intensity and method of coach contact [14].

To do this, the within-group models built in aim 1 will be used to generate potential outcomes for each couple’s likelihood of adhering as well as their gains in a (1) full coaching, (2) automated coaching, and (3) contingent coach conditions. If, in aim 1, the interaction terms result in a better RMSE, models will be constructed based on treatment assignment (ie, OurRelationship or ePREP) and coach assignment (ie, full, contingent, or automated). The estimates between the conditions for each couple’s between-group treatment differences between the full and automated coaching conditions can be understood as:

where 
[figure not shown]
 is the between-group likelihood of treatment adherence or gains for couple x, *Ŷ*(*x, Full Coach*) is the within-group likelihood of treatment adherence or gains for couple x in the full-coach condition, and *Ŷ*(*x, Contingent Coach*) is the within-group likelihood of treatment adherence or gains for couple x in the contingent coach condition [14]. These hypothetical between-group outcomes will then serve as dependent variables in a second random forest to calculate VIMP, which will identify the most powerful predictors of between-group differences. After identifying the most powerful predictors using VIMP, a multiple regression model will be estimated using the reduced set of variables to aid in the interpretation of the main effects. This process will thereby help clinicians determine which couples should be assigned to which level of coach contact.

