## Results

Data collection was completed in October 2020 and data are being prepared to be analyzed. Overall, 63.8% (286/448) of individuals completed the material in the OurRelationship coach condition, 53.8% (155/288) of couples completed the OurRelationship contingent coach condition, and 54.5% (157/288) of individuals completed the OurRelationship automated (ie, email only) condition. Similarly, 69.4% (306/441) of couples completed the content in the ePREP coach condition, 74.2% (210/283) completed the content in the ePREP contingent coach condition, and 66.2% (188/284) of couples completed content in the ePREP automated (ie, email only) condition. Currently, no other outcomes except for completion rates have been analyzed. Given the large sample size within and between conditions, the current sample is large enough to identify potential predictor variables and evaluate their prediction accuracy. This study is expected to conclude in the summer of 2022.

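### Three different criteria decide whether the two programs are modelled separately, and under the Aim 1 criterion program assignment can be dropped although completion differs by program

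*Protocol article*

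**What the plan says.** The choice between three models (one per coaching level) and six (coaching level by program) appears in three places in the Protocol article.

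- **Data Analysis Plan for Aim 1.** Model 1 lets every predictor interact with coaching and program. Model 2 will "drop all program assignment interactions (ie, resulting in only Predictor×Coaching interactions"). The null hypothesis is equal RMSE. If it is not rejected, "program assignment will be ignored resulting in 3 conditions (full, contingent, and automated coaching"). The route to six models opens with the words "If the interactions account for a significant portion of the variance". The section says that the result carries into the later aims.
- **Data Analysis Plan for Aim 2.** The split is made on this condition: "If, in aim 1, the interaction terms result in a lower RMSE, better sensitivity, or better specificity". No test is mentioned.
- **Data Analysis Plan for Aim 3.** The split is made if "the interaction terms result in a better RMSE". Again there is no test, and sensitivity and specificity are gone.

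The Aim 1 section also assigns sensitivity, specificity and the predictive values to completion and RMSE to satisfaction, although its pooling test uses RMSE for both. The Results section already gives completion for all six cells, for example "74.2% (210/283) completed the content in the ePREP contingent coach condition".

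**The concern.** One decision has three criteria, and they can disagree on the same Aim 1 output. That decision sets the structure of every later model. Completion rates by program are already known and the analyses are still to be preregistered, so the ambiguity leaves room for a choice informed by the data.

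The second problem lies within Aim 1. The two models are described as differing in program interactions. The article does not say whether Model 2 keeps a main effect of program, yet failing to reject leads to program being ignored. Absence of evidence that program modifies other predictors is no reason to remove program itself when it is a randomised factor that may shift completion directly. At stake is how well completion is predicted within each coaching level, and whether the Aim 3 contrasts between coaching levels average over programs that behave differently.

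**Working it through.** **1. The three criteria side by side**

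| Aim 1 output | Aim 1 criterion | Aim 2 criterion | Aim 3 criterion |
|---|---|---|---|
| Interaction model has lower RMSE, not significant | pool | split | split |
| RMSE unchanged, specificity better | pool | split | pool |
| Interaction model has significantly lower RMSE | split | split | split |

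The three agree in the last row only.

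**2. Completion by program (counts from Results)**

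All six printed percentages reproduce from their counts.

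| Coaching | OurRelationship | ePREP | Gap (points) |
|---|---|---|---|
| Full | 286/448 = 63.8% | 306/441 = 69.4% | 5.6 (5.55 from the counts) |
| Contingent | 155/288 = 53.8% | 210/283 = 74.2% | 20.4 |
| Automated | 157/288 = 54.5% | 188/284 = 66.2% | 11.7 |
| All | 598/1024 = 58.4% | 704/1008 = 69.8% | 11.4 |

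The denominators are individuals (for example 2 × 226 − 4 = 448), while the plan analyses couples. Intervals are therefore given at design effect 1 and at design effect 2, the latter an assumed upper bound with partners fully concordant.

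Standard error = √{D × [p₁(1−p₁)/n₁ + p₂(1−p₂)/n₂]}, where D is the design effect.

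Overall, D = 2: √{2 × [0.584 × 0.416/1024 + 0.698 × 0.302/1008]} = 0.0299, so 11.4 ± 1.96 × 2.99 gives 5.6 to 17.3.

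| Coaching | 95% CI, D = 1 | 95% CI, D = 2 |
|---|---|---|
| Full | −0.6 to 11.7 | −3.2 to 14.3 |
| Contingent | 12.7 to 28.1 | 9.5 to 31.3 |
| Automated | 3.7 to 19.6 | 0.4 to 22.9 |
| All | 7.3 to 15.6 | 5.6 to 17.3 |

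The coaching-stratified Mantel-Haenszel difference is also 11.4 points. Heterogeneity of the gap across coaching levels: Q = 8.7 on 2 df, P = 0.013 at D = 1; Q = 4.3, P = 0.11 at D = 2.

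The withdrawals listed under Participants imply denominators of 284 and 283 for the ePREP contingent and automated arms, the reverse of those in Results. The contingent rate would then be 210/284 = 73.9%, which changes nothing material.

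**3. What pooling averages over**

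Full minus contingent coaching is 63.8 − 53.8 = +10.0 points in OurRelationship and 69.4 − 74.2 = −4.8 in ePREP. Pooled, it is 592/889 − 365/571 = 66.6% − 63.9% = +2.7.

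**4. How far RMSE moves**

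If a 0/1 outcome is predicted by its mean, RMSE = √[p(1−p)]. In the contingent arm:

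- program ignored: p = 365/571 = 0.639, RMSE = √(0.639 × 0.361) = 0.480;
- program used: √{[288 × 0.538 × 0.462 + 283 × 0.742 × 0.258]/571} = 0.469.

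The reduction is 2.3%. Over all arms, six cells instead of three take RMSE from 0.4791 to 0.4747, or 0.9%. These are cell-mean predictions, not forests.

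**5. Chance splitting under the Aim 2 criterion**

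Suppose the two models are truly equal and each of the three measures is as likely to favour one as the other. The probability that at least one favours the interaction model is 50% if all three move together and 1 − 0.5³ = 87.5% if they are independent. A split takes the contingent and automated models from 288 couples each to 145 (OurRelationship) and 143 (ePREP).

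**The case against.** The strongest reply is that there is one rule, loosely repeated. Aim 1 says that its result carries forward, Aims 2 and 3 both refer back to Aim 1, and Aim 3 says that it uses the models built there. The longer list in Aim 2 may simply name the measures for the binary outcome beside the one for the continuous outcome. On that reading the article need not produce three models in one aim and six in another. What stands against it is that neither later section mentions significance, Aim 2 adds measures that the Aim 1 test does not use, and Aim 3 names RMSE alone. Even if Aim 2 is read outcome by outcome, completion would split by chance in 50% to 75% (1 − 0.5²) of cases.

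Pooling was also a reasonable question to leave open. The Introduction reports equal adherence, 69%, for the two programs in an earlier fully coached trial, and the full-coach gap here is compatible with zero. Both points stand, and they place the problem mainly in the contingent and automated arms.

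A reader might infer more than the document supports:

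- **That non-rejection is likely.** The test is not specified, and a small shift in RMSE is not a power calculation. Only the possibility is shown.
- **That the Aim 2 criterion halves the data almost whatever the truth.** The lower figure is 50%. Measures that trade off against each other would exceed the upper figure, but the article gives no basis for choosing their correlation.
- **That the two-sided alternative is a practical fault.** The accompanying words require the interactions to account for variance, which a worse-fitting model does not do.
- **That pooling defeats the study.** The abstract does aim to "create an algorithm to assign future couples to different programs and levels of coach contact", and forests without program cannot inform the first part. The aims in the body, however, concern coaching level.
- **That pooling is wrong for satisfaction.** Only completion has been analysed.

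**Conclusion.** The concern holds in two parts. First, the criteria in Aims 1, 2 and 3 differ as written and give opposite instructions for a plausible result, a lower but non-significant RMSE. Second, the Aim 1 criterion can discard program after a test of its interactions, although the article's own counts show an overall completion gap of 11.4 points, clear of zero even at design effect 2, and a contingent-arm gap of 20.4 points.

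The size rests on the printed counts, on treating them as individuals, and on a design effect between 1 and 2. The contingent gap is the largest of three, and the evidence that gaps differ by coaching level weakens to P = 0.11 at design effect 2. Six models remain available under the plan. This should be fixed before preregistration, but it does not invalidate the design.

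**What to change.** State one decision rule, apply it once in Aim 1, and have Aims 2 and 3 refer to its result without restating a criterion. The rule should split by program only if the interaction model predicts better out of sample, with an error measure suited to each outcome. The Brier score for completion and squared error for satisfaction would serve; other proper choices are equally defensible.

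Replace the statement that program will be ignored with one that keeps program assignment as a candidate predictor in every within-coaching forest, whatever the rule decides. A main effect of program can then be used without building six models.

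The cost is wording in the preregistration, which the article describes as still to come, and one extra predictor per model. No new data are needed.
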